### Analysis plan

All statistical analyses will be conducted using R^64^ (V.4.1.1.; R Core Team, Vienna, Austria) within RStudio^65^ (RStudio Team, Boston, MA).

Confirmatory hypotheses will be tested using linear mixed models, assuming approximate normality of random effects and residuals. If model diagnostics indicate substantial violations of distributional assumptions, generalised linear mixed models with appropriate link functions and distribution will be applied based on the observed characteristics of the data.

Each model will include Group as a between-subject factor and Time (10 levels, one per visit) as a within-subject factor. The Group factor represents the treatment conditions (TAU, partial reinforcement and continuous reinforcement). The number of Group levels varies by hypothesis and will be specified within each hypothesis section. Random intercepts for participants will be included to account for individual differences. Random slopes will be added if they significantly improve model fit, as evaluated by likelihood ratio tests and information criteria (ie, Akaike Information Criterion, Bayesian Information Criterion).

Main effects and Group × Time interactions will be examined depending on the respective hypotheses. Pairwise comparisons of estimated marginal means will be conducted where appropriate, with Holm-adjusted p values used to control for multiple comparisons, particularly given the unbalanced group sizes. A significance level of α=0.05 will be applied for all confirmatory tests.

#### Hypothesis 1

We hypothesise that both experimental treatments (pooled across partial and continuous reinforcement) will be non-inferior to the TAU group regarding average reductions in itch, PASI and DLQI scores from pre-measurement to post-measurement. Non-inferiority testing will be embedded within the linear mixed model framework. One-sided 95% CIs will be computed based on model estimates. Non-inferiority will be concluded if the upper bound of the CI lies below the predefined MCID of 25%.^66^

#### Hypothesis 2

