We hypothesise that symptom trajectories differ between groups. Specifically, both experimental groups are expected to show slower improvements in objective disease severity (ie, PASI scores), while improvements in subjective symptoms (ie, itch and DLQI scores) are expected to be comparable to those in the TAU group. Group × Time interactions will be modelled to identify differential symptom trajectories. Given the absence of prior data on the exact shape of these trajectories, no assumptions about their functional form are made beyond the directionality stated above. Post hoc contrasts will be conducted to explore group differences at specific time points or in change patterns across the study period.

#### Hypothesis 3

As part of hypothesis 3, we examined potential effects on secondary outcomes, namely side effects. Specifically, we hypothesise that participants in the experimental groups (pooled across partial and continuous reinforcement) will report fewer side effects from pre to post compared with the TAU group. A linear mixed model with a Group × Time interaction will be fitted to side effect scores derived from the GASE questionnaire.

#### Hypothesis 4

Supplementary to the other hypotheses, a subsequent analysis focusing on the two reinforcement groups will examine potential differences in both overall and longitudinal effects of the various dosing regimens. We hypothesise that the partial reinforcement group will show stronger treatment effects on outcomes compared with the continuous reinforcement group. Specifically, we expect significantly greater average reductions in itch, PASI and DLQI scores over time. This hypothesis will be tested via the Group × Time interaction across all 10 measurement points. If the interaction is significant, follow-up contrasts will compare the estimated change trajectories between the two experimental groups, with a focus on overall pre–post improvement and the rate of change over time.

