### Exploratory analyses

In addition to the confirmatory analyses, exploratory analyses will be conducted to examine potential associations between the primary outcomes and various secondary and moderating variables, including demographic characteristics (eg, age, gender), psychometric measures (eg, depression, anxiety), biological markers (ie, blood, saliva) and ecological momentary assessments (ie, itch ratings, treatment satisfaction). These analyses are exploratory in nature and are intended to generate hypotheses for future research.

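### Hypotheses 2 to 4 are run as confirmatory, at least seven Group × Time tests each at 5%, with no rule controlling error across outcomes or hypotheses

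*Protocol article*

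**What the plan says.** The Analysis plan opens with the confirmatory hypotheses, to be tested with mixed models, and fixes the level: "A significance level of α=0.05 will be applied for all confirmatory tests". Hypotheses 1 to 4 follow. The next section begins "In addition to the confirmatory analyses, exploratory analyses will be conducted", so the exploratory label is kept for the association analyses described there and Hypotheses 2 to 4 stay on the confirmatory side.

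The tests are:

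- **Hypothesis 2** (itch, PASI, DLQI): "Group × Time interactions will be modelled to identify differential symptom trajectories". It predicts a difference for PASI only: "both experimental groups are expected to show slower improvements in objective disease severity (ie, PASI scores". For the other two, "improvements in subjective symptoms (ie, itch and DLQI scores) are expected to be comparable to those in the TAU group".
- **Hypothesis 3** (GASE side-effect scores, pooled reinforcement arms against treatment as usual), introduced with "As part of hypothesis 3, we examined potential effects on secondary outcomes, namely side effects".
- **Hypothesis 4** (itch, PASI, DLQI, partial against continuous reinforcement), introduced as supplementary to the others: "This hypothesis will be tested via the Group × Time interaction across all 10 measurement points". Follow-up contrasts are made only if the interaction is significant.

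On multiplicity the plan says: "Pairwise comparisons of estimated marginal means will be conducted where appropriate, with Holm-adjusted p values used to control for multiple comparisons".

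The Sample size section calls the pooled non-inferiority comparison the primary hypothesis, and also says it is tested at an exploratory level.

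**The concern.** The labels and the alpha rule do not match. Hypothesis 3 concerns a secondary outcome and Hypothesis 4 is supplementary, yet both fall under the confirmatory rule at the full 5% per test. Seven tests is a minimum: itch has two ratings (worst and average), GASE yields two scores (total load and medication-attributed), and the hypotheses do not name one of either pair.

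Holm on pairwise comparisons of marginal means does not cover the interaction tests. In Hypothesis 4 there are only two groups, so Holm across group pairs adjusts nothing. No rule says whether one outcome out of three is enough.

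Hypothesis 4 is where this matters most. The Trial design section makes the continuous arm the dose control for the partial arm, and Hypothesis 4 is the only test of partial reinforcement at equal cumulative dose. As the plan stands, a favourable result on any one of three outcomes could be presented as confirmatory support for the partial schedule. Hypothesis 3 could likewise yield a confirmatory side-effect claim whatever the result on non-inferiority.

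**Working it through.** **The plan's own figure.** The article states a per-test level of 0.05 and no familywise error rate, so there is no stated figure to reproduce. The question is what familywise rate the rule implies.

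**Inputs from the article.** α = 0.05 per test. Test count: 3 (Hypothesis 2) + 1 (Hypothesis 3) + 3 (Hypothesis 4) = 7. Of these, 1 (PASI in Hypothesis 2) + 1 + 3 = 5 are tests where significance would fit a predicted difference.

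**Assumed, because the article does not give it.** Between-outcome correlation ρ from 0 to 0.9, equal among itch, PASI, DLQI and GASE. Hypothesis 2 run either as pooled arms against treatment as usual or as a three-group test. All null hypotheses true.

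**Step 1, independent tests.** P(at least one rejection) = 1 − (1 − 0.05)^k.

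- Hypothesis 4 alone, k = 3: 1 − 0.95³ = 14.3%
- Five tests, k = 5: 1 − 0.95⁵ = 22.6%
- Six tests (without PASI in Hypothesis 2, where a real difference is expected), k = 6: 1 − 0.95⁶ = 26.5%
- Seven tests, k = 7: 1 − 0.95⁷ = 30.2%

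**Step 2, correlated outcomes.** Simulation of correlated chi-square interaction tests, at least 100,000 runs per setting. The contrast of pooled arms with treatment as usual is orthogonal to that of partial with continuous, so their statistics are independent within an outcome. Each cell spans two codings of Time: 1 df (a single trend) and 9 df (ten visits as categories), doubled for the three-group form of Hypothesis 2.

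| ρ | Hypothesis 4, any of 3 | All 7, Hypothesis 2 pooled | All 7, Hypothesis 2 three-group | The 5 tests, pooled | The 5 tests, three-group |
|---|---|---|---|---|---|
| 0 | 14.2–14.4% | 30.0–30.3% | 25.0–25.6% | 22.5–22.7% | 20.8–21.0% |
| 0.3 | 13.5–13.8% | 28.7–29.1% | 23.4–24.6% | 21.9–22.1% | 19.7–20.4% |
| 0.5 | 12.6–13.0% | 26.2–27.3% | 21.8–23.1% | 20.7–21.2% | 18.7–19.4% |
| 0.7 | 11.0–11.5% | 22.5–23.7% | 18.8–20.4% | 18.4–19.2% | 16.7–17.6% |
| 0.9 | 8.5–8.8% | 16.7–17.9% | 14.5–15.9% | 14.6–15.5% | 13.5–14.5% |

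In round terms: 9–14% for Hypothesis 4, 15–30% for all seven, 14–23% for the five.

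**Step 3, direction.** Hypothesis 4 predicts that partial reinforcement does better. With the 9-df test, requiring a significant interaction and a pre–post estimate favouring partial reinforcement on the same outcome gives 7.3% at ρ = 0, 6.7% at 0.5 and 4.7% at 0.9. Requiring that pre–post contrast to be significant as well gives about 1–2%.

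**Simplification.** The 9-df figures treat every outcome as measured at ten visits. The Outcomes and Moderators sections schedule itch and GASE at visits 1 to 9 only. The effect on these rates is small.

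**The case against.** Several points on the other side stand.

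- A reader might infer a single false-claim rate of 20–25%. The article does not support that. Any such value needs a particular correlation and a particular form of Hypothesis 2, and it counts rejections, not claims. Two of the seven tests (itch and DLQI in Hypothesis 2) predict comparability, so a chance rejection there contradicts the hypothesis.
- The global null is not what the investigators expect, since Hypothesis 2 anticipates a real PASI difference.
- Hypothesis 4 sends a significant interaction to follow-up contrasts. If a significant favourable pre–post contrast is required, the false-positive rate is only about 1–2%; counting rate-of-change contrasts as well would raise it somewhat. But the plan does not say that such a contrast is required for success.
- It would be wrong to say there is no hierarchy. Hypothesis 1 is called primary, Hypothesis 3 secondary and Hypothesis 4 supplementary. This is a ranking in words, without an alpha rule attached.
- It would also be wrong to say that Holm acts only after a significant interaction and within one outcome. The plan applies it where appropriate and leaves its family undefined; gating on the interaction is stated only for Hypothesis 4.
- The 5% is a per-test level. No familywise figure is stated, so none is contradicted.
- Whether secondary hypotheses need joint error control is partly convention, and a testing order is often left to a statistical analysis plan. Here, however, the article itself fixes the rule: confirmatory status and the full 5% for every such test.
- Hypothesis 4 might be read as requiring all three outcomes, which would remove the inflation within it. The text states no such success rule.

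**Conclusion.** The concern holds in this form: Hypotheses 2 to 4 carry confirmatory status at 5% per test, the Holm rule is not stated for the interaction tests, and nothing controls the choice among itch, PASI and DLQI in Hypothesis 4 or error across the three hypotheses.

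Under a global null, the chance of at least one nominal rejection is about 9–14% for Hypothesis 4 and 15–30% for all seven tests. It is about 14–23% for the five tests where significance would fit a predicted difference. These ranges rest on assumed correlations of 0 to 0.9 and on two or three groups in Hypothesis 2. They are any-rejection rates; for Hypothesis 4 in the predicted direction the figure is about 5–7%.

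The problem is one of labelling and decision rules. It does not undermine the models or the data collection, and it should be settled before the data are analysed.

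**What to change.** In the Analysis plan:

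1. State that Hypotheses 2 and 3 are secondary, reported with estimates and confidence intervals and without a confirmatory claim.
2. For Hypothesis 4, choose one of two routes. Either label it secondary as well, or keep it confirmatory and apply Holm across its itch, PASI and DLQI interaction tests at 5% (thresholds 0.05/3 = 0.0167, then 0.025, then 0.05). A stated requirement that all three succeed would also serve. Do not make it conditional on Hypothesis 1: the equal-dose comparison is a separate question and should not be blocked if non-inferiority fails.
3. Reconcile this with the Sample size section, which describes the non-inferiority test both as primary and as being at an exploratory level, so that a reader can tell which claims carry confirmatory weight.

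The cost is wording only, with no change to conduct, sample size or data. The downside is a stricter threshold for Hypothesis 4, or loss of the confirmatory label.

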### Secondary outcomes

#### Objective symptom severity

The PASI^48^ will be used as a clinical scoring tool to assess the extent of affected body surface area and the severity of key symptoms in patients with psoriasis. As the most commonly used clinical tool for objectively evaluating psoriasis severity,^48^ the PASI provides a composite score ranging from 0 to 72, with scores of at least 10 representing a moderate-to-severe degree of psoriasis severity. The PASI will be conducted at all visits.

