### Sample size, group allocation and blinding

#### Sample size

To test the non-inferiority of the drug-dose reduction strategy to the standard care at an exploratory level, the sample size calculation was conducted in R using the epiR package (function: epi.ssninfb). This calculation is based on a non-inferiority framework using the absolute risk difference scale. For the purpose of calculation, a favourable outcome was assumed for 70% of participants in the reinforcement group and 75% in the TAU group. The non-inferiority margin was set to an absolute risk difference of 0.25, corresponding to a minimal clinically important difference (MCID) of >25%. Assuming a one-sided α=0.05 and 80% power, a total sample size of N=152 was required for a 1:1 comparison between TAU and the pooled reinforcement groups. As the primary non-inferiority hypothesis compares TAU with the pooled reinforcement groups, the sample size calculation was based on a 1:1 allocation ratio.

To account for the dropout rate of 10% during a previous study, which investigated the impact of verbal inductions of positive treatment-related expectations as a dose-reduction strategy in patients with psoriasis,^33^ a sample size of N=168 is set.

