#### Group allocation

The allocation of patients to the study groups will take place after enrolment and receipt of written informed consent. To balance disease severity between groups, the randomisation of patients will follow a stratified randomisation schedule based on PASI scores and will be carried out by the research assistant. The stratified randomisation schedule will be generated prior to study initiation by a postdoctoral researcher who is not involved in patient care, recruitment or data collection. The study physician will have no access to the randomisation list. Prior to recruitment, two strata were established based on PASI scores: 60% of patients were expected to have a PASI ≤15 and 40% a PASI of >15. Within each stratum, randomisation to one of the three intervention groups will be performed using computer-generated random numbers. These numbers will be generated using an Excel spreadsheet and will determine the respective group assignments. To ensure blinding, the group assignment will be initially blackened out, with the group only revealed after the assignment has been completed.

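### The Hypothesis 1 non-inferiority margin of 25% has no unit or denominator on the itch, PASI and DLQI scores being tested, and the plausible readings give opposite conclusions

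*Protocol article*

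**What the plan says.** The protocol article's Analysis plan, under Hypothesis 1, sets the pooled reinforcement arms against TAU "regarding average reductions in itch, PASI and DLQI scores from pre-measurement to post-measurement". It adds that "Non-inferiority testing will be embedded within the linear mixed model framework" and that "One-sided 95% CIs will be computed based on model estimates". The decision rule is: "Non-inferiority will be concluded if the upper bound of the CI lies below the predefined MCID of 25" per cent, with a literature citation attached.

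The only other place where 25% is used as a margin is the Sample size section: "The non-inferiority margin was set to an absolute risk difference of 0.25, corresponding to a minimal clinically important difference (MCID) of >25" per cent. The calculation there is for two proportions: "a favourable outcome was assumed for 70% of participants in the reinforcement group and 75% in the TAU group". The article does not define a favourable outcome, and no analysis of proportions with such an outcome appears in the Analysis plan.

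**The concern.** A linear mixed model of scores estimates a difference in mean change in VAS points, PASI points and DLQI points. A bound in points cannot be set against a bare percentage. A denominator is needed, and at least three are available: the range of the scale, the baseline score, and the TAU reduction. The one scale that is given, a difference between two proportions, belongs to a different analysis.

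This is the threshold of what the Sample size section itself calls the primary non-inferiority hypothesis. If the readings lead to different conclusions on the same data, the rule as printed does not determine the trial's answer. The rule also names the upper bound without saying which arm is subtracted from which, or whether the quantity is a change in score or a reduction.

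**Working it through.** **1. The plan's own use of 25%.** Inputs from the Sample size section: rates 0.70 and 0.75, margin 0.25, one-sided α 0.05, power 80%, 1:1 allocation. Per arm, n = (0.75×0.25 + 0.70×0.30) × (1.645 + 0.842)² / (0.25 − 0.05)² = 0.3975 × 6.183 / 0.04 = 61.4, so 62 per arm and 124 in total. The stated 152 is not reproduced. It is larger than needed, not smaller: with 76 per arm the power of that binary comparison is Φ(0.20/√(0.3975/76) − 1.645) = 87%. What matters here is that margin and power both refer to a difference in proportions. Neither carries over to a difference in mean points.

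**2. Itch, two readings.** The VAS runs from 0 to 100.
- A quarter of the range is 25 points.
- A quarter of the TAU reduction is 7.5 to 12.5 points, for an assumed reduction of 30 to 50.

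Take 76 per group (152/2), an assumed SD of change of 20, 25 or 30, a TAU reduction of 30 and a reinforcement reduction of 15, so the true loss is 15. As an approximation to the mixed model, P(pass) = Φ((margin − 15)/(SD√(2/76)) − 1.645). The standard errors are 3.24, 4.06 and 4.87.
- Margin 25: 92%, 79% and 66%.
- Margin 7.5: below 0.1% at all three SDs.

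**3. PASI, three readings.** The Objective symptom severity section states that "the PASI provides a composite score ranging from 0 to 72".
- A quarter of the range is 0.25 × 72 = 18 points.
- A quarter of the mean baseline is 3.7 to 4.9 points, for an assumed mean baseline of 14.7 to 19.5.
- A quarter of the TAU reduction is 3.3 to 4.4 points, for the same baselines and an assumed 90% reduction.

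The range reading is roughly four to five times as wide as the other two. The Group allocation section says "60% of patients were expected to have a PASI ≤15 and 40% a PASI of >15". The first of these groups could not improve by 18 points even with full clearance.

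For an arm with no improvement, the expected upper bound is f × mean baseline + 1.645 × SD × √(2/84). Here f is the TAU reduction as a share of baseline, and 84 per group is 168/2. Setting this equal to 18 with f = 0.90 gives a mean baseline of (18 − 1.27)/0.9 = 18.6 at SD 5, (18 − 1.78)/0.9 = 18.0 at SD 7 and (18 − 2.54)/0.9 = 17.2 at SD 10. Below these values the expected bound lies under 18. The threshold moves to 20.6–22.3 for f = 0.75 and 15.5–16.7 for f = 1.0.

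As pass probabilities, with 76 per group and SD 5 to 9, the non-improving arm passes 86–100% of the time at TAU reductions of 10 to 14 points, 39–79% at 16, and 5% at 18.

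**4. Direction.** Suppose TAU improves by 40 itch points and the reinforcement arms by none, with SD 25 and 76 per group. The half-width is 1.645 × 25 × √(2/76) = 6.7.
- Experimental minus TAU change in score: 0 − (−40) = +40, upper bound +46.7. The rule rejects, correctly.
- Experimental minus TAU reduction: 0 − 40 = −40, upper bound −33.3. The rule would be met by a complete failure.

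The DLQI was not worked through because the article does not give its total range.

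**The case against.** The 25% is cited to a source, and a fuller analysis plan may exist; either could supply the denominator. That is fair, and it would be wrong to infer that no denominator was ever fixed or that one will be picked after the results are seen. But the article does more than stay silent: it equates the percentage with a risk difference, and that is incorrect for the test it describes.

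A reader might infer that the PASI test lets through an arm that does not improve at all. The documents do not support this as a general statement. They never adopt the range reading, and they give neither a mean baseline PASI nor an expected TAU response. Entry requires PASI above 10, and 40% are expected above 15 with no upper limit, so larger TAU reductions, at which the test would usually reject such an arm, cannot be excluded.

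A reader might also infer that the upper bound is on the wrong side. That is not shown. Lower scores are better on all three outcomes, and for experimental minus TAU change in score the upper bound is the conventional side. What stands is that the coding is not stated and the hypothesis is worded in terms of reductions.

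Finally, the Sample size section describes the non-inferiority test as exploratory. The same section calls it the primary hypothesis, and the Analysis plan gives it a formal decision rule, so the rule should be executable.

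**Conclusion.** The point holds. The Hypothesis 1 threshold is not defined on the scale that the model estimates, and the claimed correspondence with a risk difference of 0.25 is wrong. This is an internal conflict between the Sample size section and the Analysis plan, not a detail left for later.

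The itch comparison shows that the choice of denominator alone can turn near-certain failure into a likely pass; it rests on the assumed TAU reduction of 30 points and SD of 20 to 30. The PASI result is conditional: on the range reading, the test can pass a non-improving arm if the mean baseline is below about 17–18, assuming roughly a 90% TAU reduction. The direction of the contrast is an ambiguity to close, not a demonstrated error.

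**What to change.** Before unblinding:
- State the margin for each of itch, PASI and DLQI on the scale the model estimates.
- State the contrast and its direction.
- In the Sample size section, remove the statement that the risk difference of 0.25 corresponds to this MCID, and say that the 80% power refers to the binary comparison and not to the Hypothesis 1 test.

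One option keeps the plan's 25% and its one-sided 5% level. With reductions coded so that larger is better, declare non-inferiority if the one-sided 95% lower bound of (mean reduction, pooled reinforcement − 0.75 × mean reduction, TAU) is above 0, and report the implied margin in points. Nothing in the article favours this over a justified fixed margin in points for each outcome, which would equally cure the defect.

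The text change is small, but the retention option has two costs. Its margin in points moves with the observed TAU effect. Its power may also fall short of 80%. With truly equal arms and 76 per group, power = Φ(0.25R/(SD√(1.5625/76)) − 1.645), where R is the TAU reduction. For itch at R = 30 this gives about 83%, 67% and 54% at SD 20, 25 and 30. For PASI at R = 10 and SD 9 it gives about 62%. Power is lower still if the reduced-dose arms do slightly worse, as the sample size assumptions allow. The power of whichever test is chosen should be reported.

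### The sample-size margin is a 0.25 risk difference on a binary outcome, but the planned non-inferiority test compares mean score reductions with a 25% limit that has no unit or base, so the stated 80% power does not describe that test.

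*Protocol article*

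**What the plan says.** **Sample size.** The text states that "This calculation is based on a non-inferiority framework using the absolute risk difference scale" and that "a favourable outcome was assumed for 70% of participants in the reinforcement group and 75% in the TAU group". It continues: "The non-inferiority margin was set to an absolute risk difference of 0.25", "corresponding to a minimal clinically important difference (MCID) of >25" per cent. The result is given as "Assuming a one-sided α=0.05 and 80% power, a total sample size of N=152 was required" for a 1:1 comparison of TAU with the pooled reinforcement groups, raised to 168 for dropout.

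**Analysis plan.** "Confirmatory hypotheses will be tested using linear mixed models, assuming approximate normality of random effects and residuals". Hypothesis 1 concerns average pre-to-post reductions in itch, PASI and DLQI. One-sided 95% confidence intervals come from the model, and non-inferiority is concluded if "the upper bound of the CI lies below the predefined MCID of 25" per cent. If diagnostics fail, "generalised linear mixed models with appropriate link functions and distribution will be applied based on the observed characteristics of the data".

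**Outcomes.** Itch is a 0–100 visual analogue scale and PASI runs from 0 to 72. DLQI items are scored 0 to 3. All three are scores; the article defines no favourable outcome.

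**The concern.** A linear mixed model contrast of mean reductions is in score points. A 25-percentage-point loss in the proportion with a favourable outcome is not a 25% loss in mean score, nor a loss of 25 score points. The article calls its limit predefined, yet the limit can be read as scale points, a share of the scale range, a share of baseline or a share of the TAU reduction. The choice could then be made after the data are seen, and it could decide the result.

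The stated 80% power belongs to a comparison of proportions that the article does not plan to make. It says nothing about the chance that the mixed-model test succeeds.

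The generalised-model fallback leaves the link function open and gives no margin for any scale other than the original one.

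**Working it through.** **1. The plan's own figure.** Inputs from the Sample size section: 75% (TAU), 70% (reinforcement), margin 0.25, one-sided α 0.05, 80% power, 1:1. The assumed true difference is 5 points, which leaves 0.25 − 0.05 = 0.20 to the margin.

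n per arm = [0.75×0.25 + 0.70×0.30] × (1.645 + 0.842)² / 0.20² = 0.3975 × 6.183 / 0.04 = 61.4, so 62 per arm and N = 124.

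The stated 152 is not reproduced with these inputs. One-sided α 0.025 gives 78 per arm, N = 156, which is close to 152. With 76 per arm and one-sided 0.05, power on the binary scale is 86.9%. This is a side observation: it does not harm the binary power, and the point here does not depend on it. For dropout, 152 × 1.1 = 167.2, which rounds up to 168.

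**2. The two limits side by side.**

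| | Sample size | Hypothesis 1 |
|---|---|---|
| Outcome | binary, favourable or not | itch, PASI and DLQI scores |
| Quantity | difference in proportions | difference in mean reductions |
| Limit | 0.25 absolute | 25%, unit and base not stated |

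**3. How far the readings differ (PASI).** A quarter of the range is 0.25 × 72 = 18 points. A quarter of an assumed 13-point TAU reduction is 0.25 × 13 = 3.25 points. The ratio is 18 / 3.25 = 5.5. An upper confidence bound between 3.25 and 18 points would pass under one reading and fail under the other.

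**4. Power on a score scale.** The article gives no SD, baseline mean or expected reduction. For a simple two-group comparison of change with 76 per arm and one-sided α 0.05:

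power = Φ(g / √(2/76) − 1.645), where g = (margin − true loss) / SD of change.

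80% power needs g = (1.645 + 0.842) × 0.1622 = 0.40. Other values:

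| g | 0.25 | 0.33 | 0.40 | 0.63 |
|---|---|---|---|---|
| Power | 46% | 65% | 79% | 99% |

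**5. Itch as an example.** The SDs of change, the baseline of 60 and the reductions of 40 and 30 are all assumed; true loss is 0.

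| Reading of 25% | Margin (points) | SD 20 | SD 25 | SD 30 |
|---|---|---|---|---|
| 25 scale points | 25 | ~100% | ~100% | ~100% |
| 25% of baseline 60 | 15 | 99.9% | 98% | 93% |
| 25% of TAU reduction 40 | 10 | 93% | 79% | 66% |
| 25% of TAU reduction 30 | 7.5 | 75% | 58% | 46% |

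Power therefore runs from 46% to about 100%, depending on the reading and the SD.

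**The case against.** The strongest defence is that this is a condensed article. The reference cited for the 25% limit is not at hand and may give its base, and the full protocol or analysis plan may define the favourable outcome and a margin for each score. That stands as far as missing detail goes. It does not remove the mismatch, because no later document can make a 0.25 risk difference and a limit on three mean score reductions the same quantity.

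The article also describes the non-inferiority test as exploratory. But the same section speaks of a primary non-inferiority hypothesis, and the Analysis plan places the test among its confirmatory hypotheses.

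Several stronger readings are tempting, but the documents do not support them:

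- *The readings of 25% will give opposite verdicts, and an arm with no improvement could pass.* An 18-point PASI limit does exceed the baseline of the 60% of patients expected at 15 or below. But the Analysis plan never mentions scale range, and its talk of average reductions makes a share of the reduction at least as natural. Different conclusions are possible, not shown.
- *The trial is underpowered.* Without an SD, a reduction or a score margin, power cannot be computed. The repeated measures could also lower the effective SD.
- *The fallback moves the estimate to a ratio or log-odds scale.* It may. An identity link is not excluded, and estimated marginal means are planned and can be reported in score points.
- *The 80% power is for a 25-point difference.* The 0.25 is the margin; power is computed at an assumed true difference of 5 points.

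**Conclusion.** The point holds as a contradiction between the Sample size section and Hypothesis 1. The margin and power are on a risk-difference scale, the test is on mean score reductions, and the decision limit has no unit or base. This conclusion rests on the text alone and on no assumed figure.

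Its size can only be illustrated. The PASI limit differs 5.5-fold between two readings, given an assumed 13-point TAU reduction. Illustrative itch power lies between 46% and about 100% for assumed SDs of 20 to 30. The simple two-group formula ignores any gain from repeated measures; that would change the SD but not the mismatch. Because this is the decision rule for what the article itself calls the primary non-inferiority hypothesis, it should be settled before any unblinded look at the data.

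**What to change.** Choose one of two routes and make both sections agree.

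- **(a) Score scale.** State a justified margin in score points for each of itch, PASI and DLQI. A stated fraction of the TAU reduction in the research group's earlier N=120 trial is one option; the fraction needs its own clinical justification. Define the contrast as TAU reduction minus pooled-reinforcement reduction, so that the upper bound is the relevant one. Restate the power for that contrast, with the source of the SD.
- **(b) Risk difference.** Keep 0.25, define the favourable outcome, and make the risk difference the quantity tested against 0.25.

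Under either route, if the generalised model is used, report the non-inferiority contrast on the scale of the margin, for example as marginal means back-transformed to score points under (a). Also reconcile the exploratory label in the Sample size section with that section's primary hypothesis and with the confirmatory status in the Analysis plan.

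The cost is revised wording and one recalculation. Recruitment is planned to run until 30 June 2027, so there is time. The downside is that under route (a) with a strict margin the restated power may be clearly below 80%. In the itch example with a 7.5-point margin and SD 25 it is 58%, and 80% would need N = 276. The fix is to report the restated figure openly; it does not in itself call for more patients.
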